##### Inclusion criteria for control (healthy) group

2.2.1.2

Healthy patients (without any polypoid lesions found during screening colonoscopy);Adult patients (≥18 years);Written informed consent.

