#### Procedure

3.1.2

Highly experienced endoscopists, with proven adenoma detection rate of >30% will perform the colonoscopy, endoscopic polypectomy (if needed) and tissue sampling intended for the study. In case of CRC or endoscopically unresectable polyps, experienced abdominal surgeons specializing in colorectal surgery will take over the sampling procedure, as well. Patients will undergo simple polypectomy, endoscopic mucosal resection (EMR), endoscopic submucosal dissection (ESD), transanal endoscopic microsurgery (TEM) or surgery for CRC depending on the localization, size and histology of the lesion found. Procedures are scheduled as a common management of a colorectal neoplasm and will not be affected by patient’s preliminary enrolment in the study. During colonoscopy or colon resection the mucosal biopsy specimens from the polypoid lesion and the healthy gut (macroscopically healthy right- and left-sided colon and terminal ileum) will be obtained using disposable biopsy forceps (separate for each segment) to avoid bacterial contamination. The tissue sampling plan includes a) tissue of the terminal ileum; b) tissue of the right-sided colon (cecum, ascending colon, right colic flexure); c) tissue of the left-sided colon (descending colon, sigmoid colon and the rectosigmoid junction); and d) tissue of the lesion (if present). In case of small adenomas (<1 cm size), sampling is performed near the lesion, since multiple biopsies directly from the small tumor may result in artificial material fragmentation, at the same time raising the risk of histological misdiagnosis. Hyperplastic polyps and non-polypoid lesions are not being sampled, nor resected during colonoscopy in terms of the study. If multiple diverticula are present, normal tissue of the colon will be sampled at the least affected site. More than ten locoregional polyps are considered as polyposis and are not further investigated under this trial. Otherwise, while up to ten polyps are detected in the same colon region, the largest is being picked for sampling and subsequent investigation. Inflammatory or pseudo-polyps are not adenomatous lesions, thus are not considered eligible for the study. Bowel preparation should be evaluated with at least 6 out of 9 points according to the Boston Bowel Preparation Scale (BBPS), otherwise precise detection and evaluation of dysplastic mucosal lesions cannot be ensured. Those patients who underwent colonoscopy and have been evaluated by less than 6 points according to BBPS will not be included in further study. Resected or sampled polyps should be described using the Paris and NICE classifications. Each stool and tissue sample will be encoded according to localization of the colon and the type of examination it is dedicated for.

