##### Histopathological examination and further allocation

3.1.3.1

Biopsy specimens (resected polyps and samples of normal colonic and ileil mucosa) will be fixed in 10% buffer formalin 24-48 hours at room temperature, processed and embedded in paraffin (FFPE). The FFPE sample sections will be cut at 3 μm thickness and mounted on positively charged slides. All slides will be stained with hemotoxylin-eosyn (HE) for the accurate evaluation of polyps and healthy colon histology.

Patients with non-adenomatous mucosal and sessile serrated lesions will be eliminated from the study. Only patients with histopathologically confirmed colorectal adenoma (small/large), carcinoma *in situ* and adenocarcinoma are being selected for further examination and become study participants. These patients will be divided into 4 exposure groups according to the CR neoplasia size and the dysplasia level, and 4 self-control groups (patient serves as his own control), and the general control group V as an overall healthy patients’ control (**Table 2**). Patients with macroscopically normal but histologically confirmed adenomatous or non-adenomatous mucosal lesions in control-site biopsies will not be enrolled in further examination and so will be eliminated from the study.

**Table 2 T2:** Histology- and size-based allocation of participants.

Exposure	Control
Group I (N=10): endoscopically removed and histopathologically confirmed up to 1 cm sized (low-grade dysplasia) tubular/tubulovillous/villous adenoma;	Control group 1: biopsy samples from group I patients’ terminal ileum, right- and left-sided healthy colon;
Group II (N=10): endoscopically removed and histopathologically confirmed 1 cm or greater (low- or high-grade dysplasia) tubular/tubulovillous/villous adenoma;	Control group 2: biopsy samples from group II patients’ terminal ileum, right-and left-sided healthy colon;
Group III (N=10): endoscopically removed/sampled and histopathologically confirmed Ca *in situ* (high-grade dysplasia);	Control group 3: biopsy samples from group III patients’ terminal ileum, right- and left-sided healthy colon;
Group IV (N=10): endoscopically sampled and histopathologically confirmed invasive adenocarcinoma;	Control group 4: biopsy samples from group IV patients’ terminal ileum, right- and left-sided healthy colon;
Control group V (N=10): patients, without any polypoid lesions found during colonoscopy (mucosal biopsies from their terminal ileum, right- and left-sided healthy colon).	

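### Bowel preparation is judged on a BBPS total alone, so two well-prepared segments can offset a poor one, and a control can be called lesion-free without every segment having been adequately seen

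*Protocol article*

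**What the plan says.** Section 3.1.2 (Procedure) gives one bowel-preparation criterion: "Bowel preparation should be evaluated with at least 6 out of 9 points according to the Boston Bowel Preparation Scale (BBPS"). It gives the reason at once: "otherwise precise detection and evaluation of dysplastic mucosal lesions cannot be ensured". It then restates the criterion as an exclusion: "Those patients who underwent colonoscopy and have been evaluated by less than 6 points according to BBPS will not be included in further study". Both statements concern the total score. No section of the article sets a minimum for any part of the colon.

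Controls are defined by what the examination did not find. Section 2.2.1.2 reads "Healthy patients (without any polypoid lesions found during screening colonoscopy"), and Table 2 in section 3.1.3.1 reads "Control group V (N=10): patients, without any polypoid lesions found during colonoscopy". The general exclusions in section 2.2.1.3 also apply to controls. Section 3.1 makes the comparison of lesion stages with healthy controls part of the primary outcomes.

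The sampling plan in section 3.1.2 takes biopsies from "macroscopically healthy right- and left-sided colon and terminal ileum". The right side is specified as "tissue of the right-sided colon (cecum, ascending colon, right colic flexure") and the left as "tissue of the left-sided colon (descending colon, sigmoid colon and the rectosigmoid junction"). The transverse colon is in neither list.

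**The concern.** The criterion exists so that lesions can be seen throughout the colon, but a threshold on a sum cannot guarantee that for each part. A high score in two parts can carry a low score in the third past the cut-off. The rule may then admit a patient in whom the condition it is meant to secure does not hold.

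This matters most for Group V. A lesion in a poorly seen segment would leave a patient with an adenoma labelled healthy. With 10 to 15 controls planned (section 2.2.4), a single such case is a visible share of the group. It would tend to pull control values towards those of the adenoma groups and so weaken the contrasts with healthy controls.

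The exposure groups are affected less directly. They are allocated on the lesion found, and a more advanced lesion missed elsewhere could place a patient in too early a group.

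**Working it through.** **Inputs from the article**
- Inclusion threshold: total of at least 6 out of 9 (section 3.1.2).
- Group V size: 10 in Table 2; 10 to 15 per group in section 2.2.4.

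**Assumption not in the article**
- The total is the sum of three colon segments (right, transverse, left), each scored 0 to 3, with lower scores meaning poorer visibility. This agrees with the stated maximum, since 3 × 3 = 9.

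**Step 1: patterns that qualify.** There are 4³ = 64 possible score triples. Replacing each score x by 3 − x turns a total of at least 6 into a total of at most 3, and the number of such triples is C(6,3) = 20. So 20 patterns qualify.

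**Step 2: split by the lowest segment.**
- Lowest score 0: the other two must sum to at least 6, so both are 3. This gives 3 patterns (0-3-3, 3-0-3, 3-3-0).
- Lowest score 1: the orderings of 1-2-3 give 6 and those of 1-3-3 give 3, so 9 patterns. Two segments at 1 cannot qualify, because 1 + 1 + 3 = 5.
- All segments at 2 or more: 2³ = 8 patterns.
- Check: 3 + 9 + 8 = 20. Patterns with a segment at 0 or 1: 3 + 9 = 12.

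These counts show what the rule permits. They do not weight patterns by how often they occur, and the article gives no frequencies.

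**Step 3: what the sampling plan removes.** Biopsies must come from healthy-looking right and left colon, so a segment scored 0 on either side would sit badly with the plan. Of the three patterns with a 0, that leaves mainly 3-0-3, with the transverse colon at 0. The plan takes no tissue there from a control. The 9 patterns with a segment at 1 are not removed.

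**Step 4: weight of one misclassified control.** 1/10 = 10%; 1/15 = 6.7%. Suppose that control carries the full difference Δ between the adenoma-bearing and healthy states. The expected mean contrast then falls from Δ to Δ(1 − 1/n), that is to 0.90Δ with n = 10 or 0.93Δ with n = 15. The planned tests on immune data are rank-based, so this only indicates direction and order of size.

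**Step 5: chance that Group V is touched at all.** Let p be the share of qualifying controls with an inadequately seen segment. The article gives no value, so p is assumed. The chance of at least one such control is 1 − (1 − p)ⁿ.

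| Assumed p | n = 10 | n = 15 |
|---|---|---|
| 0.5% | 4.9% | 7.2% |
| 1% | 9.6% | 14.0% |
| 2% | 18.3% | 26.1% |
| 5% | 40.1% | 53.7% |

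This is the chance of a poorly seen segment, not of a missed lesion. The latter is smaller, because the segment must also contain a lesion that goes undetected.

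**The case against.** The article does not contradict itself: the threshold is the same as an inclusion and as an exclusion rule, and no stated figure is wrong. The segment structure of the scale, the meaning of each score and any particular floor come from outside the article. A condensed article may also leave endoscopic detail to the full protocol.

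There are real safeguards. Endoscopists must have an adenoma detection rate above 30%. Obstructing tumours that prevent a complete colonoscopy are excluded. Healthy-looking right and left colon and terminal ileum must be reached and biopsied, and a lesion on histology at a control site removes the patient. Tightening the rule also costs recruits, and section 5.2 already expects Group III to be short.

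Much of this stands. The segment structure is an assumption and is labelled as one. The risk is unquantified. The safeguards make a wholly unseen right or left colon unlikely. They do not close the gap, however. A biopsy shows that a point was reached, histology reads only the tissue taken, and a detection rate describes the operator rather than the view in a given patient. The article also does not leave this rule to another document: it states the cut-off, the consequence and the purpose, so the rule can be judged against that purpose. The recruitment point is a reason to apply the change differently by group.

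**Conclusion.** The point holds in a limited form. The stated rule is total-only and, on the assumed three-segment scoring, permits 12 of 20 qualifying patterns with a segment at 0 or 1. It can therefore miss its own stated purpose. The consequence is possible misclassification in Group V, at 6.7% to 10% of the group per case, tending to dilute contrasts with healthy controls. How often this would happen cannot be estimated from the article.

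Several stronger readings are tempting and are not supported:
- That the rule generally admits colons with an unseen segment. Only 3 patterns contain a 0, each needs two perfect scores, and the biopsy plan makes two of them unlikely.
- That 12 of 20 means most admitted patients are poorly prepared. Patterns are not equally likely.
- That Group V is the reference for every primary comparison. Table 2 also sets up four self-control groups, which are a separate reference.
- That residual stool contaminates one side and weakens the right-versus-left contrast. Nothing in the article supports this, and contamination of one side could equally create a difference.

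**What to change.** In section 3.1.2, state that the three BBPS segment scores are recorded, and add a per-segment minimum to the total of at least 6 as a criterion for research inclusion, at least for Group V. A minimum of 2 in each segment is one example. That value is an assumption for the investigators to confirm, as is the segment structure itself. If the full protocol already has a segment criterion, the article needs only to say so.

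For exposure groups where recruitment is tight, Group III in particular, keep the patients and plan a sensitivity analysis that leaves out those with any segment below the chosen minimum.

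The change is a sentence or two. On the assumed scoring, the segment scores already exist, because the total is their sum. Patient care is unaffected, since section 3.1.2 says that procedures do not depend on enrolment. The downside is a small, unquantified number of extra screening exclusions.

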
#### Post-procedure

3.1.3

The pseudonymized stool and tissue samples will be labelled with unique study ID and transferred to the hospital’s microbiological laboratory or biobank where they will be frozen at the − 80°C refrigerator for later use. A part of intestinal tissue samples will be assessed immediately for histological evaluation and immunohistochemically for AI-based DIA. Stool samples and mucosal biopsies will be simultaneously examined for fecal and mucosa-associated microbiota. Thereafter, data analysis on microbial composition and its alterations in both fecal and gut tissue specimens will be performed, compared, and correlated. Another part of the collected colon mucosal samples will be contained in a biobank for future study on intestinal epithelial cell oncogenic mutations and its interrelation with intestinal immunity and gut microbiome in the light of colorectal carcinogenesis.

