### Data collection and management

3.1

Assessment of participants will be conducted at the pre-procedure (-t1), procedure (0) and post-procedure (t1-t4) timepoints. The detailed schedule of assessments is depicted in **Table 1**. The primary outcomes will be the differences in the microbiota composition and immune infiltration in different localizations of the tumor and different steps of mucosa dysplastic lesions compared to healthy controls. The secondary outcomes include correlation analysis of gut microbial diversity, intestinal immunity variables and the grade of colorectal dysplasia assessed for the study.

**Table 1 T1:** Study schedule of enrolment, interventions, and assessments.

	STUDY PERIOD						
	Enrolment	Allocation	Examination and analysis period				Close-out
TIMEPOINT	*-t_1_ *	0	*t_1_ *	*t_2_ *	*t_3_ *	*t_4_ *	*t_x_ *
ENROLMENT:							
Eligibility screen	X						
Informed consent + filling the questionnaire	X						
Allocation		X					
INTERVENTIONS:							
Collection of fecal samples	X	X					
Colonoscopy + endoscopic polypectomy (or biopsy) and normal gut tissue sampling or right hemicolectomy and gut tissue sampling	X		X				
ASSESSMENTS AND DATA ANALYSIS:							
Pathologic investigations: HE and IHC	X	X	X				
16S rRNA gut tissue- and fecal-derived microbiota sequencing			X	X	X	X	
AI-based digital image analysis			X	X	X	X	
Qualitative data analysis based on the questionnaires		X	X				
Data analysis on intestinal immune infiltration variables: count, density, and distribution of CD3, CD8, CD20, CD68 cells in epithelial and stromal compartments				X	X	X	X
Data analysis on gut microbiota compositional changes in tissue and stool samples: relative abundance, α- and β-diversity, etc.				X	X	X	X
Correlation analysis of gut microbiota and immune response variables in different site of the colon along the adenoma-carcinoma sequence						X	X

X, mark the appropriate period for the enrollment, interventions and other activities during the project

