##### Immunohistochemistry and AI-based digital image analysis of intestinal mucosal tissue

3.1.3.2

Immunohistochemical staining will be performed using the Roche Ventana BenchMark ULTRA (Ventana Medical Systems, USA) automated slide stainer. Monoclonal antibodies against B lymphocytes (CD20), T lymphocytes (CD3), cytotoxic T-lymphocytes (CD8) and macrophages (CD68) will be used.

HE, CD3, CD8, CD20, CD68 slides will be scanned using a ScanScope XT Slide Scanner (Leica Aperio Technologies, CA, USA) or an Aperio 18 AT2 Slide Scanner (Leica Microsystems, Wetzlar, Germany) with 20x magnification (0.5 μm resolution). Digitized whole-slide images will be archived in a pathology image database ImageScope (version 11.1.2.752, Leica Biosystems, Chicago, USA), then transferred to a DIA platform HALOTM (version 2.2.1870, Indica Labs, New Mexico, USA).

The intestinal immune system response will be examined using digital pathology image analytics. Primarily, IHC procedures for the visualization of the immune cell markers (CD3, CD8, CD20 and CD68) will be developed and optimized to fit the requirements of DIA. Multiplex IHC will be used to enhance the analysis where both cell populations with specific biological properties and their spatial interactions at the cellular and regional level in tissue microenvironment are included. Then, digital image processing procedures will be established for the robust immune cell infiltrate quantification and analysis of spatial distribution patterns in the intestinal tissues. Analysis of cell population (CD3, CD8, CD20, CD68) will be completed by employing HALO Multiplex IHC module. The methodology that combines DIA, artificial intelligence tools and based on explicit rules will be employed.

The analysis workflow follows: 1) the training of artificial intelligence-based HALO AI classifier to segment the intestinal tissues into classes (stroma, non- malignant epithelium, malignant epithelium etc.); 2) the detection and quantification of immune cell counts/densities in epithelial and stromal compartments. Finally, immune cell population distribution and interaction patterns will be correlated to the composition of the gut microbiota and pathology features. The findings will enable us to generate informative combinatorial models to achieve more precise prediction of CRC development.

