### Limitations of the study

5.2

The single-centre type of this study could be a limit, potentially exposing to recruitment biases. The efforts to avoid selection bias could also be hindered by the fact that sessile serrated lesions as the alternative pathway of colorectal carcinogenesis are not being examined. The study could also be hampered due to the restricted examination of mainly bacterial microbiota composition. The sample size of about 50 participants nevertheless responds to 190 sampling sites, 570 tissue specimens and 50 stool samples being examined for microbiota and local immunity structures, therefore, is not considered small, especially in the light of human gut microbiota studies (63). Due to expected lower incidence of Ca *in situ* lesions in the population, the study has a risk of being limited by the lack of samples in III exposure group. However, in that case the risk could be mitigated by relocating exposure groups and representing adenoma-carcinoma sequence in the form of subsequent dysplasia examination from small (early) and large (advanced) adenomas as initial stages and invasive carcinomas (Ca *in situ* and adenocarcinoma) as the progression of the disease.

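### Study IHC is placed around each patient's procedure and slides may go to either of two scanners, so stain run and scanner can be unevenly spread across disease groups, and the planned tests cannot account for this

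*Protocol article*

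**What the plan says.** All references are to the protocol article.

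- **Timing.** Section 3.1.3 (Post-procedure) states: "A part of intestinal tissue samples will be assessed immediately for histological evaluation and immunohistochemically for AI-based DIA". In Table 1 (section 3.1), the row "Pathologic investigations: HE and IHC" is marked at -t1, 0 and t1, while image analysis runs from t1 to t4.
- **Staining procedure.** Section 3.1.3.2 says: "Primarily, IHC procedures for the visualization of the immune cell markers (CD3, CD8, CD20 and CD68) will be developed and optimized". No point is named after which the procedure no longer changes.
- **Scanner.** The same section says: "slides will be scanned using a ScanScope XT Slide Scanner (Leica Aperio Technologies, CA, USA) or an Aperio 18 AT2 Slide Scanner". No rule says which slides go to which model.
- **Recruitment.** Section 5.2 warns that "the study has a risk of being limited by the lack of samples in III exposure group", because carcinoma in situ is less common.
- **Analysis.** Section 4 compares immune cell counts and densities between groups with Kruskal-Wallis followed by Dunn's test, at p < 0.05.
- **Outcome.** Section 3.1 makes differences in immune infiltration across lesion steps and against healthy controls part of the primary outcome. Correlation with dysplasia grade is secondary.

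**The concern.** Automated tissue segmentation and cell detection work on the digitised image, so stain intensity and scanner characteristics are inputs to the outcome. If staining follows each patient's procedure, the stain run depends on when the patient was recruited. If one group fills later than the others, its slides come disproportionately from later runs and perhaps from the other scanner. A technical shift then looks like a difference between stages.

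Kruskal-Wallis and Dunn take no covariate, so the analysis as stated cannot remove the shift. With about 10 patients per group, a modest shift is enough to disturb the error rate. How far it can be repaired afterwards depends on how uneven the spread became and on whether run and scanner were recorded.

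**Working it through.** **1. The plan's own counts (section 2.2.4).** Four lesion groups of 10 patients with 4 sites each, and 10 controls with 3 sites: 40 × 4 + 10 × 3 = 190 locations. The stated 570 samples imply 570 / 190 = 3 per location. With four antibodies, 570 × 4 = 2280 specimens. The stated figures reproduce.

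**2. What 10 per group can detect.** No effect size is stated. Solving back from n = 10 per group, two-sided alpha 0.05 and 80% power gives d = 1.32 for a two-group t-test, or f = 0.51 for a five-group ANOVA.

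**3. Spurious difference.** Let *b* be the early-to-late (or scanner-to-scanner) shift in SD of cell density, and let *p3* and *p0* be the late shares in Group III and in each other group. With no true group difference,

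spurious difference = *b* × (*p3* − *p0*).

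- 30% versus 80%: 0.5 × 0.5 = 0.25 SD; 1.0 × 0.5 = 0.50 SD.
- 20% versus 100%: 0.5 × 0.8 = 0.40 SD; 1.0 × 0.8 = 0.80 SD.
- 0% versus 100%: 0.50 SD and 1.00 SD.

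The values of *b*, *p3* and *p0* are assumptions. The documents give none of them.

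**4. False-positive rates.** Simulation with five groups of 10, normal data, no true difference and 8,000 replicates. The pairwise test is an unadjusted Mann-Whitney of Group III against one other group, standing in for Dunn. The complete-alignment row is a separate simulation of two groups only, using the exact test.

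| Late share, others / Group III | Shift (SD) | Kruskal-Wallis | Pairwise |
|---|---|---|---|
| any of the first three patterns below | 0 | 0.040–0.049 | 0.040–0.045 |
| 50% / 50% | 0.5; 1.0 | 0.033; 0.016 | 0.039; 0.025 |
| 30% / 80% | 0.5; 1.0 | 0.053; 0.079 | 0.065; 0.124 |
| 20% / 100% | 0.5; 1.0 | 0.093; 0.261 | 0.117; 0.320 |
| 0% / 100% (complete) | 0.5; 0.8; 1.0 | not run | 0.152; 0.360; 0.520 |

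A check of the pairwise test with 200,000 replicates agrees: 0.066 and 0.123 for 30% / 80%; 0.113 and 0.325 for 20% / 100%; 0.162, 0.353 and 0.513 for complete alignment.

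**5. Does the remedy work?** The 50% / 50% row shows that balance across groups keeps both tests at or below 0.05. For 30% / 80% with a 1.0 SD shift, a linear model with a batch term gives 0.054 (4,000 replicates). Adjustment therefore works under partial imbalance, provided run and scanner were recorded. It fails only when a group shares no run with any other.

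**The case against.** **Optimisation comes first.** Section 3.1.3.2 is written as a sequence: IHC procedures are optimised, then image processing is set up. A reader might infer that study slides are stained under changing versions of the procedure. The text does not say so, and that reading is not adopted here. What stands is that no lock point is named, and that differences between runs and scanners remain even under a fixed procedure.

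**The timing is not truly patient by patient.** In section 3.1.3 the word immediately contrasts with tissue frozen for later, and section 3.1.3.1 requires fixation, HE and histological confirmation before allocation. Table 1 has no dates. This leaves room for batched IHC. Even so, the sentence covers IHC for the image analysis, and Table 1 marks it early. Followed as written, staining tracks recruitment.

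**Only Group III is said to be scarce.** This is correct. That controls and ordinary adenomas fill early would be inference. Section 5.2 also plans to merge carcinoma in situ with adenocarcinoma if Group III falls short. That would dilute a late-staining shift in the merged group, not remove it.

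**Each patient is their own control.** This largely protects lesion versus own normal tissue if those slides share a run and scanner. It would be wrong to treat every comparison drawn from the 2280 specimens as exposed.

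**A laboratory manual or SAP may handle runs.** It may, and silence on run layout is not the point. The point rests on choices the article does state: immediate IHC, either scanner, and tests without a covariate. The fixed automated stainer, the common scanning resolution and the single analysis platform limit the shift but do not tie runs to a balanced layout.

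**Sequencing.** A reader might extend the concern to 16S because Table 1 spreads it over t1 to t4. The samples are frozen at −80°C for later use, and stool and mucosa are to be examined simultaneously. The text shows no defect there.

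**Conclusion.** The concern holds as a design risk. As written, stain run and scanner can be unevenly spread across disease groups, and the planned tests would read any resulting shift as a group difference. Exposed are the contrasts between stages, those with healthy Group V, and the correlations with dysplasia grade.

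The size is unknown. For assumed shifts of 0.5 to 1.0 SD, the pairwise false-positive rate is about 7–12% (Kruskal-Wallis 5–8%) under a 30% / 80% imbalance and 12–32% (Kruskal-Wallis 9–26%) under 20% / 100%. The 15–52% range needs complete alignment of run with group, which is the worst case and which nothing in the document predicts. For the same reason, the stronger statement that later analysis could not separate run from stage is not supported: under partial imbalance, a recorded batch term separates them.

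The change is still worth making, because it must precede staining and costs little.

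**What to change.** 1. Keep immediate HE for diagnosis and allocation.
2. Hold the paraffin blocks already planned in section 3.1.3.1. Do the study IHC after the staining procedure is locked, in runs balanced across the groups, with all sites of one patient in the same run where capacity allows.
3. Scan every slide on one named scanner model. If both must be used, balance them across groups and keep each patient's slides on one.
4. Record run and scanner for every slide so that they can be adjusted for.
5. As a secondary safeguard for 16S, spread the groups across DNA extraction and sequencing plates and record the plate.

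**Cost.** No extra patients, biopsies or study slides are needed. IHC results come later, at or near the end of recruitment. Run capacity needs checking, since the document does not give it. One patient per group with all sites is 4 × 4 + 3 = 19 locations, or 19 × 3 × 4 = 228 slides (57 per antibody). If that exceeds a run, keep each patient's slides together and mix the groups as evenly as possible within and across consecutive runs.
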